### Sample size

2.5

Based on the annual incidence of STS cases managed at the surgical center, a total of 50 patients will be recruited. Given the current absence of evidence regarding personalized rehabilitation in this population, the obtained results will be exploratory and will serve as a basis for determining the appropriate sample size in similar future trials.

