### Baseline assessment

2.6

Once the written informed consent is acquired, a baseline assessment will be conducted for each patient. Concerning patient’s demographic and clinical characteristics, the following data will be collected.

Demographics (e.g., age, gender, height, mass);Past medical history;Tumor site;Histopathological tumor characteristics;Tumor staging;Information on adjuvant and/or neoadjuvant therapies and surgery;Medications taken;Functional impairments evaluated through the Musculoskeletal Tumor Society Rating Scale differentiated for the Lower Limb (MSTS-LL) Enneking et al. (15). This scale includes six domains regarding pain, functions, emotional acceptance, use of an external aid, walking, and lifting capabilities: it provides a total score ranging from 0% to 100% with higher values indicating better functional status;Activity limitations evaluated through the Toronto Extremity Salvage Score differentiated for the Lower Limb (TESS-LL) Davis et al. (16). It contains 30 questions assessing how difficult daily activities are (e.g., mobility, working, and wearing) execution on a scale from 0 (i.e., impossible to perform) to 5 (i.e., no difficulty). The final score ranges from 0% to 100% with higher values indicating better function;Pain evaluated through the Numerical Rating Scale (NRS) Downie et al. (17) and the Brief Pain Inventory (BPI) Cleeland and Ryan (18). The former quantifies pain in adult with a score ranging from 0 (no pain) to 10 (worst pain imaginable), the latter assesses pain intensity and its interference with daily activities with a score ranging from 0 to 10 with higher values indicating more severe pain and greater functional impairment. In addition, the neuropathic pain will be evaluated through the Douleur Neuropathique en 4 Questions (DN4) Bouhassira et al. (19) and the Leeds Assessment of Neuropathic Symptoms and Signs (LANSS) Bennett (20). The former includes 10 items: seven are related to patient-reported symptoms (i.e., burning, painful cold, electric shocks, tingling, needles, numbness, and itching) and three to clinical examination (i.e., hypoesthesia to touch, hypoesthesia to pinprick and pain provoked by brushing). Each positive answer scores 1 point, with a total score ranging from 0 to 10: a score of 4 or higher is indicative of neuropathic pain. The latter allows the discrimination between the nociceptive pain and the neuropathic one, combining subjective questions regarding symptoms (e.g., burning sensations, tingling, electric shocks) and objective sensory tests (e.g., changes in sensitivity to touch or pinprick). It provides a total score ranging from 0 and 24 with a value greater than 12 indicating a significant neuropathic component to the pain. From a general perspective, the use of the NRS, BPI, DN4 and LANSS will allow a granular characterization of the patient’s pain, including intensity, impact on activities and qualitative sensory descriptors;The perceived QoL evaluated through the Short Form Health Survey 36 (SF-36) Ware Jr (21) and the European Organisation for Research and Treatment of Cancer Quality-of-Life Questionnaire (EORTC QLQ-C30) Aaronson et al. (22). The former comprises 36 items evaluating eight health domains QoL (i.e., physical functioning, role functioning, bodily pain, general health, vitality, social functioning, role emotional and mental health) with a score ranging from 0 to 100 with higher values indicating a better QoL. The latter focuses on five functional domains (i.e., physical, role, emotional, cognitive, and social), QoL and eight symptom-related dimensions (i.e., fatigue, nausea and vomiting, pain, dyspnea, insomnia, loss of appetite, constipation, diarrhea, and financial difficulties) with each item scored on a scale from 0 to 100. Higher values in the functional domains and QoL indicate better well-being, whereas higher values in the symptom scales reflect a greater symptom burden.

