*T_0_* (within 7 days before surgery): an analysis of the patient’s demographic and clinical characteristics will be carried out in order to define the most suitable surgical approach. Then, a clinical survey composed of MSTS-LL, TESS-LL, NRS, BPI, DN4, LANSS, SF-36, and EORTC-QLQ-C30 will be adopted to evaluate the patient functional impairments, activity limitations during daily activities, pain and QoL at the beginning of the study;*T_1_* (within 7 days post-surgery): the aforementioned clinical survey will be submitted to the patient to evaluate the surgery’s short-term effects on functional impairments, activity limitations during daily activities, pain, and QoL;*T_2_* (within 30 days post-surgery): the clinical survey will be submitted to the patients to evaluate the clinical status before the beginning of the rehabilitation treatment. Moreover, the patients’ ambulation capabilities during free overground walking will be analyzed as soon as the patient is able to walk. Gait analysis will be conducted using the optoelectronic, marker-based BTS Smart D 500 system (BTS Bioengineering, Milan, Italy) within a calibrated acquisition volume of 5 × 3 × 2 m³. Before to each session, eight cameras will be mounted on tripods and geometrically calibrated; twenty-two 10-mm photo-reflective markers will be positioned on specific anatomical landmarks according to the Davis protocol Davis III et al. (25). Kinematic data will be acquired at a sampling frequency of 100 Hz. Kinetic parameters will be collected through two P-6000 force platforms (BTS Bioengineering, Milan, Italy) at a sampling rate of 1000 Hz. Surface electromyography will be recorded using eight FREEEMG sensors (BTS Bioengineering, Milan, Italy) applied to the following muscles of the operated limb: 1) Rectus Femoris responsible for hip flexion and knee extension, 2) Vastus Lateralis responsible for hip flexion and knee extension, 3) Vastus Medialis responsible for hip flexion and knee extension, 4) Biceps Femoris responsible for hip extension and knee flexion, 5) Semitendinosus responsible for hip extension and knee flexion, 6) Gluteus Maximus responsible for hip extension, 7) Tibialis Anterior responsible for ankle flexion, 8) Gastrocnemius Lateralis responsible for ankle extension. These muscles were selected because they are superficial and play a primary role in physiological gait Barbero et al. (26). Electrode placement will follow the recommendations of the Surface EMG for the Non-Invasive Assessment of Muscles guidelines Hermens et al. (27). Myoelectric signals will be sampled at 1000 Hz. Whether access to the anatomical landmarks or muscle bellies is limited due to wound healing, medical dressings or other clinical constraints, alternative strategies will be considered based on the patient’s condition and the requirement for accurate measurement. The markers may be positioned over bandages when necessary, and EMG sensors may be placed as close as possible to the target muscle belly while respecting clinical safety and feasibility. During each session, the patients will complete ten barefoot walking trials at a self-selected speed along an 8.0 m straight walkway. When walking aids (e.g., unilateral crutch, cane, or walker) will be required, the same aid will be consistently used across all assessment sessions to ensure standardization of testing conditions;

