#### Primary analysis

2.12.1

The primary endpoint will be assessed by comparing the TESS-LL score at *T_0_*and *T_3_*using a non-parametric test for paired samples (e.g., Wilcoxon signed-rank test). In addition, the primary endpoint will be used to classify the patients as responders (a change in TESS-LL score greater than 7 points) or non-responders. Subsequently, baseline clinical data that will be significantly different between responders and non-responders will be adopted as inputs for multivariate logistic regression models aiming to investigate potential predictors of recovery.

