#### Secondary analysis

2.12.2

The data obtained from the clinical questionnaires will be compared using parametric (e.g., ANOVA) or non-parametric (Friedman test) tests, as appropriate. The data obtained through gait analysis at *T_2_*will be compared with those at *T_3_*using parametric (e.g., t-test for paired samples) or non-parametric tests (e.g., Wilcoxon signed-rank test), according to the data characteristics and distribution.

The significance p level will be 0.05, and corrections will be executed in case of multiple comparisons among groups of data.

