## Conclusion

4

This study aims to deeply evaluate and objectively quantify the effects of a personalized rehabilitation treatment following STSs surgical treatment on patients clinical characteristics, sensorimotor performance and QoL.

Up to a maximum of fifty patients will be recruited and assessed at four time-points: baseline, post-surgery, pre- and post-rehabilitation. The rehabilitation will combine conventional physiotherapy with robotic technologies and it will be delivered over two daily sessions for 60 days. The assessments will include gait analysis, clinical scales and patient-oriented questionnaires.

The expected results will hold significant implications. First, they will provide objective evidence on the short- and mid-term functional outcomes of STS surgery. Second, the study will support the development of personalized rehabilitation pathways identifying prognostic factors related to tumor location, surgical approaches and patient characteristics. Third, the adopted structured methodology and multidisciplinary approach will serve as a reproducible model for future trials in similar rare and complex diseases.

Nonetheless, the study will be affected by limitations. The study period will be limited to three months, restricting the possibility of retrieving long-term recovery. The adopted approach will prevent the evaluation of emerging modalities such as telerehabilitation, which could improve accessibility and continuity of care. Furthermore, the lack of nutritional and genetic assessments will limit the capacity to explore biological determinants of recovery.

Future investigations should therefore extend follow-up, integrated digital and remote rehabilitation solutions and consider both genetic and nutritional assessment.

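### Predictors of recovery are chosen by univariate significance and refitted in a logistic model on the same patients, at most 50, so noise variables are likely to enter and estimates will be inflated

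*Protocol article*

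**What the plan says.** Primary analysis (2.12.1) classifies patients as "responders (a change in TESS-LL score greater than 7 points) or non-responders", using the T0 to T3 change. It then fixes how predictors are chosen: "baseline clinical data that will be significantly different between responders and non-responders will be adopted as inputs for multivariate logistic regression models". The stated aim is to look for predictors of recovery.

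Sample size (2.5): "Based on the annual incidence of STS cases managed at the surgical center, a total of 50 patients will be recruited". The Conclusion (4) treats this number as a ceiling: "Up to a maximum of fifty patients will be recruited and assessed at four time-points". Section 2.5 also labels the results exploratory.

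The significance level appears only under Secondary analysis (2.12.2): "The significance p level will be 0.05, and corrections will be executed in case of multiple comparisons among groups of data". No correction method is named there, and the predictor screen is not mentioned.

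The candidates have to be inferred from Baseline assessment (2.6), which begins "Demographics (e.g., age, gender, height, mass);Past medical history;Tumor site;Histopathological tumor characteristics;Tumor staging" and goes on to therapies, surgery, medications and the scales. Section 2.7 confirms that at T0 "a clinical survey composed of MSTS-LL, TESS-LL, NRS, BPI, DN4, LANSS, SF-36, and EORTC-QLQ-C30 will be adopted".

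On use of the output, the Conclusion expects the study to support rehabilitation pathways by "identifying prognostic factors related to tumor location, surgical approaches and patient characteristics". The Discussion expects large prognostic value for long-term function.

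**The concern.** A variable that enters a model because it passed a significance test in the same data carries a biased estimate. It was kept because its observed difference was large, and the confidence interval from the refit ignores that choice. With many candidates and few patients, some noise variables pass and many real predictors fail. The article gives no predictor list, no limit on terms, no shrinkage and no internal validation. An article may leave such details to a fuller document, but here the selection rule itself is stated, and it is a poor one.

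There is a second, structural problem. T0 TESS-LL is a baseline candidate and is also subtracted to form the change that defines response. Patients with a low T0 score by chance tend to rise, so T0 TESS-LL is linked to response even when it predicts nothing.

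At stake is the credibility of the prognostic factors that the Conclusion lists among the expected results.

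**Working it through.** The sample of 50 is a caseload figure with no effect size, SD, power or responder rate behind it, so there is no calculation in the plan to reproduce. What follows tests the stated rule.

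**Inputs**
- Patients: 50 at most (2.5 and 4).
- Screening level: 0.05 (2.12.2), taken as two-sided and uncorrected.
- Responder rate: not stated; assumed 20% to 50%, so the smaller outcome class has 10 to 25 patients.
- Candidates, low count: 4 demographics + 6 clinical items (history, site, histopathology, staging, therapies and surgery, medications) + 8 instruments = 18.
- Candidates, high count: 10 + 7 function and pain scores (BPI as two, assumed) + 8 SF-36 domains + 15 QLQ-C30 scales (5 functional, 1 QoL, 9 symptoms named) = 40. Counting neoadjuvant therapy, adjuvant therapy and surgery separately gives 42.

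**Independent noise candidates.** Expected false selections = 0.05k; P(at least one) = 1 − 0.95^k.
- k = 18: 0.9 and 60%.
- k = 40: 2.0 and 87%.
- k = 42: 2.1 and 88%.

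**Simulation of the rule on pure noise.** n = 50, normal candidates with common correlation 0, 0.3 or 0.5, responder rate 20%, 30% or 50%, t-test screen, logistic refit, 1,500 runs per setting:

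| | k = 18 | k = 40 |
|---|---|---|
| At least one noise variable enters | 40–63% | 58–88% |
| At least one Wald p < 0.05 in the final model | 19–52% | 20–73% |
| Mean apparent AUC, given any entry (true 0.50) | 0.71–0.77 | 0.72–0.81 |

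The low ends of the first two rows belong to correlation 0.5. A separate simulation gave 37–63% entry for 18 candidates and 59–90% for 42. The AUC is shown only to illustrate the optimism, since the plan contains no discrimination measure.

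**Information available.** Patients in the smaller class per screened candidate: 10/18 = 0.6 to 25/18 = 1.4 for k = 18, and 10/40 = 0.25 to 25/40 = 0.6 for k = 40. At an assumed 10 per parameter, a pre-specified logistic model supports 10/10 = 1 to 25/10 = 2.5 parameters.

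**Real predictors.** For a true difference of 0.5 SD, the t-test noncentrality is 0.5 × √(n1·n2/50). That is 0.5 × √8 = 1.41 with 10 responders and 0.5 × √12.5 = 1.77 with 25. Power at 0.05 is 28% to 41%. At a Bonferroni level it is 5% to 10% (0.05/18) or 3% to 6% (0.05/40).

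**Bonferroni screen on noise** (n = 50, 30% responders, 3,000 runs). At least one noise variable enters in 3.6% to 5.0% of studies. When one does, apparent AUC is still 0.78 to 0.80.

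**T0 TESS-LL as a candidate.** Assumed: mean 75 and SD 15 at both T0 and T3, no mean change, no ceiling, response = rise above 7. T0 TESS-LL passes the 0.05 screen in 95% of simulated studies at a T0–T3 correlation of 0.3, 82% at 0.5 and 53% at 0.7.

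**The case against.** The strongest reply is that the sentence supplying the 0.05 level also promises corrections, and that responders against non-responders is a comparison of groups. If a Bonferroni correction covered the screen, false entry would fall to about 5%. This stands as a condition on the size of the problem. It does not remove the problem: the sentence sits under the secondary analysis, names no method and is not tied to the screen. Nor would it cure the inflation in what passes, and it would lose most real predictors of moderate size.

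The candidate count is also an inference. The plan speaks only of baseline clinical data, and a fuller document may restrict the list. The instruments overlap (four pain tools, two quality-of-life questionnaires), so independence is the least realistic case. Some candidates are categorical. A Fisher exact test on a binary variable has true size of 0.9% to 4.3% for prevalence 10% to 50% and 14 to 25 responders, so t-tests throughout somewhat overstate false entry. All of this stands and is why a wide range is given.

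Section 2.5 calls the results exploratory, and that softens the fault. The Discussion and Conclusion then go further than the label allows.

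A reader might infer that the trial will nearly always report a false predictor. That would need about 40 independent candidates and no correction, and the document fixes neither. A reader might also infer that the plan will publish an inflated AUC, but it plans none. Nor is it right to say that the screen drops confounders: the study is uncontrolled and this model estimates no exposure effect.

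**Conclusion.** The point holds. The selection rule is stated in 2.12.1 and is unsound for at most 50 patients. With an uncorrected 0.05 screen, at least one noise variable enters in roughly 40% to 90% of null studies, and the estimates that pass are inflated. T0 TESS-LL tends to pass through regression to the mean alone, in about 53% to 95% of simulated studies.

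These figures rest on assumed candidate counts (about 18 to 42), correlations (0 to 0.5), responder rates (20% to 50%) and T0–T3 correlations (0.7 to 0.3). They describe how likely the outcome is; they do not make it certain. If the correction in 2.12.2 were Bonferroni and covered the screen, false entry would be about 5% and missed predictors would become the main failure.

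The paired T0 to T3 test of TESS-LL is not affected by this rule. The change should be made, but the primary comparison does not depend on it.

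**What to change.** In 2.12.1, remove the significance screen and name the predictors in advance.

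- **Preferred:** a linear model for continuous T3 TESS-LL, adjusted for T0 TESS-LL, with a short list of further T0 predictors chosen on clinical grounds (for example age and tumour site). Adjusting for T0 deals with the coupling, and the continuous outcome avoids the loss of information at the 7-point cut.
- **If the responder model is kept:** one or two pre-specified terms with Firth penalisation. A T0 TESS-LL coefficient in that model should not be read as prognostic without noting regression to the mean.
- **If a wider search is wanted:** ridge or lasso over all listed candidates, with bootstrap optimism correction that repeats the whole selection.

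Keep the list to variables known at T0, as the plan intends. T2 TESS-LL and post-operative radiotherapy arise after surgery and are not baseline predictors.

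In 2.12.2, state which comparisons the multiplicity correction covers and by what method. In the Discussion and Conclusion, describe the predictor results as hypothesis-generating, in line with 2.5.

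The cost is revised wording and a little more programming, with no added patients or visits. Fewer predictors will be claimed. The change should be made before outcome data are examined.

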#### Secondary analysis

2.12.2

The data obtained from the clinical questionnaires will be compared using parametric (e.g., ANOVA) or non-parametric (Friedman test) tests, as appropriate. The data obtained through gait analysis at *T_2_*will be compared with those at *T_3_*using parametric (e.g., t-test for paired samples) or non-parametric tests (e.g., Wilcoxon signed-rank test), according to the data characteristics and distribution.

The significance p level will be 0.05, and corrections will be executed in case of multiple comparisons among groups of data.

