## Introduction

1

Soft Tissue Sarcomas (STSs) are rare malignant tumors that account for 1% of adult solid cancers Gamboa et al. (1). Their annual incidence is estimated at approximately 24000 and 13500 new diagnoses in the European Union and the United States of America, respectively Gamboa et al. (1) Stiller et al. (2).

The clinical management of STSs is hindered not only by their rarity, but also by their biological diversity. Indeed, the World Health Organization recognizes more than one hundred histological and molecular variants, each displaying distinct pathological and clinical traits Jo and Fletcher (3). In addition, the STSs could develop in virtually any anatomical site, with the majority occurring in the limbs (60%), where the lower extremities are affected about three times more often than the upper ones Borghi and Gronchi (4), followed by the trunk (19%), retroperitoneum (15%) and head and neck (9%) Cormier and Pollock (5) Ebrahimpour et al. (6).

Although the STSs treatment generally considers both patient-related factors (e.g., age and comorbidities) and tumor-specific elements (e.g., histology, dimension and anatomical site), the combination of surgical excision and adjuvant therapies such as radiotherapy Haas et al. (7) or chemotherapy Maruzzo et al. (8) remains the reference standard Chowdhury et al. (9). The recommended radical resection requires excision of the tumor along with a margin of surrounding healthy tissue Casali et al. (10) creating large soft tissue defects which require additional reconstructive plastic surgery treatments Brunetti et al. (11).

Although effective from a reconstructive perspective, these operations compromise lower limbs sensorimotor functions inducing structural impairments (e.g., reduced joint movement, gait abnormalities), activity and social restrictions, and finally a reduction of Quality of Life (QoL) Gerrand and Furtado (12). Nonetheless, no studies have been conducted in this direction Andrews et al. (13).

Therefore, this study aims to deeply evaluate and objectively quantify the effects of a personalized rehabilitation protocol following STSs surgical treatment on clinical characteristics, sensorimotor performance, and QoL.

The paper is organized as follows: Section II describes the details of the experimental study, while Section III discusses the proposed clinical trial. The conclusions and future steps are exposed in Section IV.

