G-EO System (Reha Technology, Olten, CH): end-effector robot characterized by a body weight support and two footplates placed on a double crank and a rocker gear system, inducing locomotor gait pattern;Lambda (Lambda Health System, Yverdon-les-Bains, CH): end-effector robot for rehabilitation of patients with lower limb neuromotor disabilities. The patient sits in a chair and is secured distally by two footplates supporting single and multi-joint movements in passive, assisted or active mode;Walker View (TecnoBody, Dalmine, IT): an auto-adaptive instrumented treadmill. The robot will support the patients’ body weight and will adapt the speed according to the patient’s residual motor capabilities. In addition, the patient will be immersed in a virtual reality environment that could enhance the engagement during the session;Hunova (Movendo Technology, Genova, IT): a stabilometric platform training the patients’ equilibrium and posture in a sitting or standing position.

In accordance with Italian standards on inpatient rehabilitation, the proposed approach will not be limited to robotic treatment but will also incorporate traditional one where the motor exercises will be performed or assisted by physical therapists, mostly in one-to-one sessions.

As reported in **Figure 1**, the following four evaluation sessions will be planned throughout the duration of the study:

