
• *T_3_*(within 90 days post-surgery): the evaluations carried out in the previous session will take place in order to assess the impact of the personalized rehabilitation treatment and of the entire study on patients clinical characteristics, motor performance, and QoL.

The first two evaluation sessions will be carried out at the surgical center, while the remaining ones will be held at the rehabilitation center.

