#### Secondary endpoint

2.10.2

The secondary endpoint of the study will be the improvement over time of the patient’s clinical status and trunk and lower limb biomechanics.

The former will be evaluated through the use of the presented clinical scales and patient-oriented questionnaires; the latter will be quantified through the aforementioned gait analysis. The parameters adopted to quantify the patients’ ambulation performance will be: *i)* the stance/swing phase, gait cycle duration, step length, stride length for both limb as well as the corresponding symmetry indices computed as described in Demofonti et al. (28). The step width, walking speed and cadence will also be evaluated regardless the limb side; *ii)* the trunk and both lower limb joints kinematics along the sagittal plane. Therefore the trunk, hip, knee and ankle flexion/extension will be evaluated and the related ranges of motion will be quantified; *iii)* the vGRF exerted on the ground by both limbs and the related peak values, loading rates and symmetry indices Demofonti et al. (28); *iv)* the myoelectric activity of the muscles of the operated limb and the related Root Mean Square values. The Co-Contraction Index values will be assessed for the agonist-antagonist muscle pairs RF/BF and TA/GL Infarinato et al. (29). The eventual presence of correlation between the gait indicators and the quality of life parameters will be evaluated.

During data analysis, the authors would consider a sub-group comparison on the basis of STS location (i.e., thigh anterior, medial or posterior compartment) or the resected muscles.

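### The secondary endpoint is improvement on the clinical scales, but the only test named for them is a non-directional ANOVA/Friedman comparison, and no visit pair or direction is fixed as deciding improvement

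*Protocol article*

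**What the plan says.** The endpoint in section 2.10.2 is directional: "The secondary endpoint of the study will be the improvement over time of the patient’s clinical status and trunk and lower limb biomechanics". Clinical status is to be measured with the scales and questionnaires.

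Section 2.7 announces that "the following four evaluation sessions will be planned throughout the duration of the study", and the same survey is given at each:

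- T0, within 7 days before surgery.
- T1, within 7 days after surgery: "the aforementioned clinical survey will be submitted to the patient to evaluate the surgery’s short-term effects on functional impairments".
- T2, within 30 days after surgery: "the clinical survey will be submitted to the patients to evaluate the clinical status before the beginning of the rehabilitation treatment".
- T3, within 90 days after surgery, "in order to assess the impact of the personalized rehabilitation treatment and of the entire study on patients clinical characteristics, motor performance, and QoL".

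The analysis of the scales in section 2.12.2 is a single sentence: "The data obtained from the clinical questionnaires will be compared using parametric (e.g., ANOVA) or non-parametric (Friedman test) tests, as appropriate". The section closes with: "The significance p level will be 0.05, and corrections will be executed in case of multiple comparisons among groups of data".

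The other outcomes have named visit pairs: T0 against T3 for the primary endpoint (section 2.12.1) and T2 against T3 for gait (section 2.12.2). The scales have none.

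**The concern.** ANOVA for repeated measures and the Friedman test share one null hypothesis, that scores are alike at every visit compared. The protocol gives reason to expect that null to be false before rehabilitation begins, since the introduction states that "these operations compromise lower limbs sensorimotor functions inducing structural impairments". A fall at T1 that never recovers can reject it just as a genuine recovery can. A significant result therefore does not show improvement.

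The correction clause suggests that pairwise tests will follow. It leaves open which pairs, in which direction, and which one decides. Two things are then at stake. Rebound from the acute post-operative state could be presented as improvement over time. And if all six visit pairs share the correction, the T2-T3 comparison, the one that spans rehabilitation, loses power in a sample fixed by case volume at 50 (section 2.5).

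**Working it through.** The plan has no power figure to reproduce; section 2.5 sets 50 patients from annual incidence.

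**Inputs from the protocol article.** n = 50 (2.5); four visits (2.7); significance level 0.05 (2.12.2); surgery expected to worsen function, size not given (introduction).

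**Assumptions.** Normal scores with SD 1; equal correlation ρ of 0.3, 0.5 or 0.7 between visits; post-surgical drop of 0.3 to 1.0 SD; complete data on all 50. Higher scores mean better here; for pain and symptom scales the sign reverses.

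**1. Does the omnibus test separate improvement from its absence?** Visit means (0, −d, −d, −d): a drop at T1 and no recovery. Simulation A used 1,000 trials per cell; simulation B is an independent repeat. Each range covers ρ = 0.3 to 0.7.

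| Drop d | Friedman (A) | ANOVA (A) | Simulation B |
|---|---|---|---|
| 0 (no change) | 4.5–5.8% | 4.9–6.3% | – |
| 0.3 SD | 35–68% | 45–81% | 33–78% over both tests |
| 0.5 SD | 76–99% | 87–99.8% | Friedman 77–99%, ANOVA 88–99.6% |
| 0.8 SD or more | at least 99% | 100% | – |

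The two simulations agree to within a few points. Both tests hold their level when nothing changes. A steady decline across the four visits, 0.5 SD in total, also rejects: Friedman 63–95%, ANOVA 75–99%. So rejection is common when patients only get worse.

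**2. Does a named contrast behave?** In the no-recovery patterns, a T2-T3 paired t-test signals improvement in 1.6–3.2% of trials (nominal 2.5% in that direction). T0-T3 signals improvement in 0.0% and worsening in 45–100%.

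**3. Does corrected pairwise follow-up suffice by itself?** For T2-T3 in the no-recovery pattern, yes: with Bonferroni over six pairs, false improvement is at most about 0.7%. For T1-T3 it does not. Take means (0, −0.5, 0, 0): patients are back at baseline by T2 and flat through rehabilitation. The paired t-test has noncentrality

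λ = d·√n / √(2(1−ρ)).

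At ρ = 0.5 the SD of the difference is √(2 × 0.5) = 1, so λ = 0.5 × √50 = 3.54, against a two-sided critical value of about 2.75 at 0.05/6 with 49 degrees of freedom. Power is 78%. At ρ = 0.3 it is 60% and at 0.7 it is 96%; simulation B gave 55–95%. T1-T3 would thus often show a corrected, favourable difference although nothing changed during rehabilitation and nobody exceeded baseline.

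**4. What does wide correction cost?** Take a true T2-T3 gain of 0.4 SD at ρ = 0.5: λ = 0.4 × √50 / 1 = 2.83. Power of the Wilcoxon signed-rank test under Bonferroni, by simulation:

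| Contrasts sharing 0.05 | Level for T2-T3 | Power |
|---|---|---|
| 1 | 0.05 | about 77% |
| 2 | 0.025 | about 67% |
| 3 | 0.0167 | about 62% |
| 6 | 0.0083 | about 52% |

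The paired t-test gives 79% for one contrast and 54% for six. At ρ = 0.3 the Wilcoxon figures for one and six are 63% and 34%; at ρ = 0.7 they are 94% and about 79%.

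**The case against.** The strongest reply is that an omnibus test followed by corrected pairwise tests is ordinary practice, and that the correction clause points to it. A reader might infer that the plan will declare improvement from a significant ANOVA or Friedman result. The protocol never says so, and the rejection rates in step 1 are correct rejections of a false null, not type I errors of the plan. A reader might also infer that significance on almost every scale is assured by the operation. That is unsupported: no drop size is given, 0.3 SD leaves rejection well short of certain, and the introduction does not establish a sizeable drop on each pain and quality-of-life domain.

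Other parts of the reply also stand:

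- Section 2.12.2 does not list the visits for the scales. Four is inferred from section 2.7, and ANOVA is offered as an example.
- Detecting the effect of surgery is itself an aim (section 2.1), so a comparison that includes T1 has a purpose.
- Gait is measured only at T2 and T3, so its named pair does not show that T2-T3 is the one right contrast for the scales. T0-T3 is the primary endpoint's contrast and also fits the stated purpose of T3.
- Bonferroni over six pairs is an assumption. Holm over six would give about 66% instead of 52% power when the other visits differ by 1 SD (means 0, −1, −1, −0.6; ρ = 0.5).
- The study is exploratory and makes no power claim.

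It may also be said that follow-up contrasts belong in the full protocol or analysis plan, which are not shown. That covers the choice of correction method. It does not cover the mismatch in the text: a directional endpoint paired with a non-directional test, and a follow-up clause under which T1-T3 could pass for improvement.

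**Conclusion.** The point holds in limited form. The test named for the scales does not answer the secondary endpoint, and nothing in the text fixes which pair or direction does. With 50 patients and ρ of 0.3 to 0.7, the omnibus test would reject with no recovery in about 33–78% of trials for a 0.3-SD drop and about 77–99% for 0.5 SD. If all pairs are followed up with no deciding contrast, T1-T3 could show improvement in 55–95% of trials, even after six-pair Bonferroni, when a 0.5-SD drop has reversed before rehabilitation. Sharing the correction over six pairs would lower T2-T3 power from about 77% to 52% for a 0.4-SD gain at ρ = 0.5.

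Drop, gain, correlation and the Bonferroni scheme are all assumptions. The conclusion that the test is non-directional and the deciding contrast unnamed depends on none of them.

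**What to change.** In section 2.12.2, name three planned paired contrasts for each scale, each reported with its estimate and 95% CI:

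- T2-T3: change over rehabilitation.
- T0-T3: change over the whole study, consistent with the primary endpoint.
- T0-T1: short-term effect of surgery.

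State the favourable direction for each scale, and claim improvement only from T2-T3 or T0-T3 in that direction. Apply the multiplicity correction within each scale to these three contrasts only, and keep the ANOVA/Friedman result as descriptive.

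The cost is wording: no new visits or data. The other three pairs (T0-T2, T1-T2, T1-T3) become descriptive. Correcting over three contrasts still costs some T2-T3 power compared with a single contrast (about 62% against 77% in the example), but less than six-pair Bonferroni. In an uncontrolled study T2-T3 still includes natural recovery, so it measures change during rehabilitation and not its effect; the report should say so.
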